# The Growth Hormone Deficiency (GHD) Reversal Trial: effect on final height of discontinuation versus continuation of growth hormone treatment in pubertal children with isolated GHD—a non-inferiority Randomised Controlled Trial (RCT)

**DOI:** 10.1186/s13063-023-07562-z

**Published:** 2023-08-21

**Keywords:** Isolated growth hormone deficiency, Growth hormone, Final height, Early puberty, Reversal, Endocrine, Early retesting, Discontinuation of growth hormone, Adverse effects, Cost effectiveness

## Abstract

**Background:**

Growth hormone deficiency (GHD) is the commonest endocrine cause of short stature and may occur in isolation (I-GHD) or combined with other pituitary hormone deficiencies. Around 500 children are diagnosed with GHD every year in the UK, of whom 75% have I-GHD. Growth hormone (GH) therapy improves growth in children with GHD, with the goal of achieving a normal final height (FH). GH therapy is given as daily injections until adult FH is reached. However, in many children with I-GHD their condition reverses, with a normal peak GH detected in 64–82% when re-tested at FH. Therefore, at some point between diagnosis and FH, I-GHD must have reversed, possibly due to increase in sex hormones during puberty. Despite increasing evidence for frequent I-GHD reversal, daily GH injections are traditionally continued until FH is achieved.

**Methods/design:**

Evidence suggests that I-GHD children who re-test normal in early puberty reach a FH comparable to that of children without GHD. The GHD Reversal study will include 138 children from routine endocrine clinics in twelve UK and five Austrian centres with I-GHD (original peak GH < 6.7 mcg/L) whose deficiency has reversed on early re-testing. Children will be randomised to either continue or discontinue GH therapy. This phase III, international, multicentre, open-label, randomised controlled, non-inferiority trial (including an internal pilot study) will assess whether children with early I-GHD reversal who stop GH therapy achieve non-inferior near FH SDS (primary outcome; inferiority margin 0.55 SD), target height (TH) minus near FH, HRQoL, bone health index and lipid profiles (secondary outcomes) than those continuing GH. In addition, the study will assess cost-effectiveness of GH discontinuation in the early retesting scenario.

**Discussion:**

If this study shows that a significant proportion of children with presumed I-GHD reversal generate enough GH naturally in puberty to achieve a near FH within the target range, then this new care pathway would rapidly improve national/international practice. An assumed 50% reversal rate would provide potential UK health service cost savings of £1.8–4.6 million (€2.05–5.24 million)/year in drug costs alone. This new care pathway would also prevent children from having unnecessary daily GH injections and consequent exposure to potential adverse effects.

**Trial registration:**

EudraCT number: 2020-001006-39

## Background

Around 500 children are diagnosed with growth hormone deficiency (GHD) every year in the UK, of whom 75% have idiopathic, isolated GHD (I-GHD) [1]. Children are treated with daily growth hormone (GH) injections until final height (FH) is reached, at an annual cost of £10,000–£23,000 per child [2]. However, when these children are re-tested after having reached their FH, between 64 and 82% are found to be producing sufficient endogenous GH [3–16], i.e. their GHD has reversed. Children with a normal pituitary on brain MRI and partial GHD are more likely to reverse. However, it is not unusual for children with structural abnormalities of the pituitary gland to also reverse [10, 12]. The underlying reasons for this reversal are largely unknown but may be explained by (1) late maturation of the GH axis or (2) difficulties inherent in the original diagnostic process.

To make the diagnosis of I-GHD in a short child, the National Institute for Health and Care Excellence (NICE) recommends at least two GH stimulation tests. These tests measure the peak GH concentration in the blood following an injection with a stimulating substance such as glucagon or insulin, and I-GHD is diagnosed if both show a peak GH < 6.7 μg/L [formerly 20 mU/L] [17]. However, a large number of GH stimulation tests are used in routine practice, and there is no consensus as to which is optimal for either diagnosing GHD or predicting a later GHD reversal [18]. Diagnostic test protocols also vary between institutions.

A number of studies have shown that sex steroid priming improves the response to provocative testing [19–21]. However, sex steroid priming is by no means universally used [22]. Additionally, studies have shown that the peak GH response is inversely correlated to weight within a cohort of normal weight children [23]. This study by Stanley et al. suggested that even normal children with a weight of + 1SDS may show a blunted GH response. Given all of these variables, it may not be surprising that the GH stimulation test itself could be associated with a high false positive rate and that re-testing after a suitable period, or at the end of GH treatment, may produce normal results, implying a reversal of GHD. This may be due to an effect of sex steroid or perhaps even loss of weight and improved body mass index.

Although I-GHD is known to reverse in many children, traditional practice is to continue treatment with daily injections of GH until FH is achieved. Establishing normal GH status in early puberty would relieve patients from the diagnostic uncertainty of GHD persistence and may allow patients to stop GH therapy earlier whilst still reaching a normal FH. This would relieve them of the unpleasant and inconvenient burden of daily injections of an unnecessary medication and considerably reduce health care cost [2].

This phase III, international, multi-centre, open label, randomised, controlled, non-inferiority trial will assess the safety, efficacy, health-related quality of life, cost effectiveness, biochemical and bone health effects of discontinuing GH therapy in children who have a normal GH re-test in established puberty. The acceptability of the trial and treatment pathways to patients, parents and staff will be explored via a qualitative research sub-study.

## Methods/design

### Aim

A)To assess whether children in established puberty with early GHD reversal who stop growth hormone therapy (GH −) achieve no worse near final height standard deviation scores (FH SDS) (primary outcome), target height (TH) minus near final height (FH), health-related quality of life (HRQoL), bone health index and lipid profiles (secondary outcomes) than those continuing growth hormone (GH +).B)To determine the cost-effectiveness of GH − in the early re-testing scenario and the cost-effectiveness of the new care pathway (early re-testing) compared to traditional care (late re-testing).C)To assess staff, parent and patient perspectives of the trial pathways and reasons for declining to participate or dropping out of the trial.

### Study design

The study design is as follows: phase III, international, multicentre, open-label, randomised controlled non-inferiority trial, including an internal pilot study, qualitative sub-study and within-trial cost analysis. The duration of the trial will be 90 months, including a 12-month pilot phase.

### Sub-studies

#### Health economics

A health economic analysis will be conducted in UK patients to determine the cost-effectiveness of GH discontinuation in the early re-testing scenario in the UK National Health Service (NHS) setting by estimating the cost per percentage of children achieving TH of GH − compared to GH + and the cost-effectiveness of the new care pathway (early re-testing) compared to traditional care (late re-testing).

#### Qualitative research

We will conduct qualitative research with UK carers, children and staff participating in the internal pilot study. The main aim of the qualitative research is to ensure the feasibility and acceptability of the trial for patients, carers and clinicians, with a particular focus on recruitment processes. These data will provide useful insights into carers’ and children’s preferences for treatment and help optimise the main trial processes. This research will explore carers’ and children’s perceptions in relation to re-testing normal (i.e. GHD reversal), reasons for agreeing to or declining trial participation, reactions to treatment allocation and associated recruitment and retention during the internal pilot. Data collection will include audio-recordings of recruitment consultations and interviews with carers, children and staff.

We will consent staff at UK recruiting sites and potential trial participants (children and carers) to audio-record recruitment consultations. Recording recruitment consultations will provide valuable data concerning how the trial and treatment groups are presented by staff and how this is received by potential participants and their carers. Following consent, semi-structured interviews will be conducted with a sample of carers and children participating in both arms of the pilot study (*n* ≈ 20–24), as well as carers and patients who decline to take part in the trial (*n* ≈ 8–10). We will undertake interviews with site PIs and staff who are recruiting patients to the trial. These interviews will take place early in the pilot phase at all UK sites that are open to recruitment so that we can understand their perspectives on the trial and the GHD re-testing pathway and understand early experiences and perspectives regarding recruitment to the trial.

Children recruited to the pilot and their carers will be interviewed at two time points: T1—approximately 2 weeks after randomisation—and T2—approximately 6 months following randomisation. Where possible, interviews will be conducted at a time and place preferred by participants. Separate interviews will be conducted with the carers and the children themselves, unless children wish to be interviewed whilst their carers are present.

T1 and decliner interviews will focus on the recruitment process, children’s motivations for taking part or not in the trial and specific barriers and facilitators to patient participation. In addition, T1 and decliner interviews will also explore children’s and carers’ experiences of GHD and its impact on their daily lives, their understanding and expectations of GHD testing and treatment options and their expectations for the trial. T2 interviews will explore children’s and their carers’ experience of the trial and treatment options and of related trial processes and procedures.

Data collection and analysis will proceed iteratively until the research team judge that the data and sample size have sufficient depth and breadth [24]. Analysis of audio-recordings will target key components of discussions regarding trial participation using thematic and conversation analysis techniques [25]. A thematic analysis of interview content will be informed by the framework analytical approach [26].

### Consent and recruitment

Children with I-GHD reversal under the care of a paediatric endocrinologist and/or a general paediatrician will be recruited from 12 UK and 5 Austrian centres. Administration of GH medication will be stopped for a minimum of 6 weeks prior to a GH re-test being performed in line with local protocols. If the patient is thought to be eligible after GH retesting, the clinical team will send the participant information sheet (PIS) to the patients’ parent/guardian, and they will be invited into clinic to discuss potential participation in the trial. It will be the responsibility of the principal investigator (PI) or their delegate to ensure written informed consent is obtained for each participant and/or parent/guardian prior to performing any trial-related procedures. The responsibility for obtaining consent may be delegated by the PI to another clinician as captured on the GHD Reversal Trial site signature and delegation log. If the potential participant and/or parent/guardian are willing to take part in the trial (and meet all of the eligibility criteria), they will be asked to sign and date the latest version of the GHD Reversal Trial informed consent form (ICF) and Assent Form if appropriate and the child will be randomised to one of the study arms. The participant and/or parent/guardian will give explicit consent for the regulatory authorities, members of the research team and or representatives of the sponsor to be given direct access to the participant’s medical records as required. This will be specified on the ICF.

We will request consent for review of participants’ medical records and for the collection of blood samples to assess serum IGF-1 and lipid profiles (fasting lipids − serum triglyceride and serum total cholesterol) and peak stimulated GH.

### Inclusion and exclusion criteria

#### Inclusion criteria

Children aged 8–15 years of age (inclusive) for females and 9–17 years of age (inclusive) for males with reversed I-GHD (peak GH ≥ 6.7 μg/L using arginine or insulin tolerance test and a serum IGF-1 within normal reference range for sex and age), normal brain MRI (including small anterior pituitary) and in established puberty (Tanner stages B2/3 in girls and 6–12 ml testes* in boys (as measured by orchidometer**)The initial diagnosis of I-GHD will have been made by either two GH stimulation tests (peak GH < 6.7 μg/L) or one stimulation test (peak GH < 6.7 μg/L) with IGF-1 below normal range for sex and age (< -2SDS) irrespective of sex-hormone priming for GH stimulation testsChildren will have discontinued GH treatment for a minimum of 6 weeks prior to re-testingAbility to tolerate the administration of GH therapyAbility to comply with trial schedule and follow-up

Written informed consent obtained from the patient’s parent/guardian and written assent obtained from patient (where age appropriate). In the UK, patients aged 16 years or older will provide their own written informed consent.

*In the event of discrepancy between the size of an individual’s testicles, the larger testicle should be used.

**In the event that the size of a patient’s testicle falls between the measuring beads of the orchidometer and it is not clear which bead the testicle is most similar to, the larger bead should be used.

#### Exclusion criteria

Multiple pituitary hormone deficiency (hypopituitarism) with or without additional pituitary hormone supplementationKnown genetic cause of I-GHDOrganic GHD (mid-brain tumours, congenital mid-brain malformations, septo-optic dysplasia; radiotherapy to the total body or brain)Ectopic posterior pituitaryOther indications for GH therapyReceiving GH treatment at any time between the (minimum 6-week) GH discontinuation period prior to retesting and randomisationReceiving prednisolone or dexamethasone at any time during the (minimum 6-week) GH discontinuation periodKnown history of persistent non-compliance with prescribed medication regimensPregnant or lactatingAny malignancyCurrently participating in another Clinical Trial of an Investigational Medicinal Product (CTIMP)

#### Randomisation

Following confirmation of patient eligibility, receipt of informed consent and completion of all questions and data items on the randomisation form, the patient will be randomised at the level of the individual in a 1:1 ratio to either continue (GH +) or discontinue (GH −) growth hormone therapy. Randomisation will be provided by a secure online randomisation system at Birmingham Clinical Trials Unit (BCTU). A minimisation algorithm will be used within the online randomisation system to ensure balance in the treatment allocation over the following variables:Tanner stage (B2 (females) or 6– < 9 ml testicular volume of the largest testicle (males) vs B3 (females) or 9–12 ml testicular volume (males).Sex (male vs female).Participating centre.

Following randomisation, a confirmatory e-mail will be sent to the responsible clinician including the child’s trial number and treatment allocation.

#### Planned interventions

Participants in the control arm (GH +) will resume receiving their GH treatment at a dosing level determined by their clinical care team (following the minimum 6-week discontinuation period required prior to randomisation). Participants in the experimental arm (GH −) will not resume GH treatment. Both arms will be followed up at 6 monthly intervals until near FH or the 36-month follow-up (whichever is soonest).

All currently available GH treatment preparations with the active ingredient Somatropin are allowed, as detailed in the British National Formulary for Children (BNFc) in the UK and Kindermedika in Austria (https://kindermedika.at/monographie/10222/somatropin).

### Trial schema (Fig. 1) and study visit schedule (Fig. 2)

**Fig. 1 Fig1:**
[figure not shown]
Trial schema

**Fig. 2 Fig2:**
[figure not shown]
GHD Reversal Trial schedule of assessments. Three asterisks (***) indicate the following: patients will be followed up until ‘Near FH (growth rate < 2 cm/year and bone age of 14 and 16 for males and females respectively). Given the usual duration of pubertal growth until FH is reached, 3 years follow-up has been allowed for; however, if patients do not reach near FH by 3 years, this may be longer

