#### Study procedures

Routine retesting in established puberty is routine clinical practice in all trial sites. Children with GHD persistence at retesting will restart GH; those with GHD reversal will be offered study participation. Following consent, participants will be randomised to GH + (25–35 µg/kg/day) and GH − groups and followed in routine endocrine clinics until ‘Near FH’ (growth rate < 2 cm/year) is reached. In the GH − group, any unexpected decrease in IGF-1 concentrations below − 2 SD (lower limit of normal) at 6 months would trigger a repeat GH stimulation test and recommencement of GH if deficient.

The baseline visit for all patients will include confirmation of inclusion and exclusion criteria, informed consent/assent, randomisation and allocation of trial number, prescription of growth hormone (if randomised to continue treatment), a record of the preparation and dose prescribed, a record of concomitant medication and relevant medical history. Height, weight and Tanner stage will also be measured at baseline. All patients will have 6-monthly visits to measure height, weight, Tanner stage, serum IGF-1 (at 6 months and annually thereafter) as well as checking compliance with GH therapy and any concomitant medication and adverse event reporting. HRQoL will be measured using the CHU9D questionnaire at baseline and at each 6-monthly visit. A left hand X-ray will be conducted at enrolment and near FH, for central analysis using the BoneXpert software. Fasting lipids will be measured at baseline and near FH.

At near FH, all subjects will have a GH stimulation test to reconfirm GH status. Given the usual duration of pubertal growth until near FH is achieved, we have allowed for 3 years follow-up.

The information captured at the randomisation and subsequent visits are shown in Fig. 2.

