### Outcome measures

#### Primary outcome

The primary outcome is as follows: near final height in standard deviation score (FH SDS).

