### Planned final analyses

The primary analysis for the trial will occur once all participants have either fulfilled the near FH definition (growth rate of < 2 cm/year and have reached a bone age of 14 years (females) or 16 years (males)), have completed the 36-month assessment or have withdrawn from the study or been lost to follow-up and corresponding outcome data have been entered onto the trial database and validated as being ready for analysis. All other outcome measure analyses will be undertaken when the final participant (as defined above) reaches their 36-month assessment.

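### Near final height, on which the primary outcome rests, is defined inconsistently: two sections assign the bone-age thresholds to opposite sexes, and a third gives no bone age

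*Protocol article*

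**What the plan says.** The Primary outcome section names the endpoint as "near final height in standard deviation score (FH SDS". What counts as near final height is stated in three places in the protocol article.

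- Fig. 2 footnote (schedule of assessments): a growth rate below 2 cm/year and "bone age of 14 and 16 for males and females respectively".
- Study procedures: participants are "followed in routine endocrine clinics until ‘Near FH’ (growth rate < 2 cm/year) is reached", with no bone-age condition.
- Planned final analyses: "growth rate of < 2 cm/year and have reached a bone age of 14 years (females) or 16 years (males".

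On the bone-age film, Study procedures says: "A left hand X-ray will be conducted at enrolment and near FH, for central analysis using the BoneXpert software".

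Two further statements matter. Under Missing data and sensitivity analyses, a child who has not reached near final height enters the primary analysis with the height from the end-of-study visit, and a sensitivity analysis leaves such children out. Planned interventions ends follow-up at near final height or 36 months, whichever comes first, whereas the Fig. 2 footnote allows follow-up to run beyond 3 years.

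**The concern.** The Fig. 2 footnote and the Planned final analyses section cannot both be applied. One gives 14 to boys and 16 to girls; the other gives 14 to girls and 16 to boys. This is not the normal condensation of a journal article, because both places state the rule in full and the rules are incompatible. Nor is it a product of the missing figure, because the footnote is legible.

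Near final height does a good deal of work in this trial. It fixes when the primary height is taken and when follow-up ends. It is part of the condition that releases the primary analysis, and it decides who is excluded from the sensitivity analysis. The bone-related secondary outcomes are measured at or up to that point, adverse-event reporting ends there, and the confirmatory GH stimulation test is done there. The trial is also open-label, so an ambiguous rule would be interpreted by staff who know the allocation. The primary endpoint should not depend on which section a reader happens to consult.

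**Working it through.** **The plan's own figure.** The sample size is not in dispute, but it was checked to see whether the definition enters it. Inputs from Sample size and power calculation: margin 0.55, SD 0.9, one-sided alpha 0.025, power 90%, true difference 0.

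n per group = 2 × (1.960 + 1.282)² × 0.9² / 0.55² = 2 × 10.51 × 0.81 / 0.3025 = 56.3, rounded up to 57. The total is 114, and 114 / (1 − 0.17) = 137.3, rounded up to 138. All three stated figures reproduce, and no bone-age threshold enters the calculation.

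**The definitions side by side.**

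| Place in the article | Growth rate | Bone age, boys | Bone age, girls |
|---|---|---|---|
| Fig. 2 footnote | below 2 cm/year | 14 | 16 |
| Study procedures | below 2 cm/year | none given | none given |
| Planned final analyses | below 2 cm/year | 16 | 14 |

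Difference, Planned final analyses minus Fig. 2 footnote: boys 16 − 14 = +2 years; girls 14 − 16 = −2 years.

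**Who is classified differently.** Read each value as a minimum to be reached. The Planned final analyses section says so; for the footnote it is an assumption. Take a child who already meets the growth-rate criterion.

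- Bone age below 14: not at near final height under either bone-age version, in either sex. Growth rate alone would count this child.
- Bone age 14 to just under 16, boy: at near final height by the footnote, not by Planned final analyses.
- Bone age 14 to just under 16, girl: not at near final height by the footnote, but at near final height by Planned final analyses.
- Bone age 16 or more: at near final height under every version, in either sex.

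The two bone-age versions therefore disagree only for slow-growing children in the band from 14 to just under 16, but they disagree for every such child.

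**What follows for those children.** A boy in the band, handled by the footnote, ends follow-up with that height. An analyst using Planned final analyses would regard him as not having reached near final height: his height still enters the primary analysis, but the sensitivity analysis drops him. A girl in the band, handled by the footnote, stays in follow-up and may contribute a later height, although Planned final analyses already counts her as having reached the endpoint.

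**The case against.** The strongest reply is that the practical effect is limited. Every version requires growth below 2 cm/year, so bone age matters only once growth has slowed. A child not at near final height still contributes a height to the primary analysis. The discrepancy applies equally to both arms, and sex is a minimisation variable. The growth-rate-only wording in Study procedures is a parenthesis in narrative text and may be shorthand for the fuller rule. Sites work from Protocol V2.0, which is not shown, so whether they see the same discrepancy is unknown. All of this stands, and it limits the consequence. It does not remove the contradiction between two full statements of the rule.

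Three stronger readings are tempting but not supported.

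- A reader might infer that no X-ray is available before near final height has to be declared. The text says "A left hand X-ray will be conducted at enrolment and near FH". The second film can be the one that confirms bone age once growth has slowed, and the Fig. 2 grid that would list all films is not shown.
- A reader might infer a one-sided bias against the discontinuation arm, through a temporary slowing of growth after GH is stopped. No section describes such slowing, and nothing in the definitions differs by arm.
- A reader might want to attach a misclassification rate to the growth-rate-only version. That needs a measurement error, a true growth rate and the interval over which velocity is calculated. The article gives none of these, and the answer depends heavily on the interval.

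**Conclusion.** The point holds as an internal contradiction in the definition behind the primary outcome. The bone-age thresholds in the Fig. 2 footnote and in Planned final analyses are assigned to opposite sexes, 2 years apart in each, and Study procedures gives no bone age at all. As written, the rule cannot be applied consistently to slow-growing children with a bone age from 14 to just under 16.

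Its consequence is bounded for the reasons conceded above. It cannot be put into SDS against the 0.55 margin, because the article gives neither the distribution of bone age when growth slows nor the growth remaining afterwards. The bound on follow-up time is itself not firm, since Planned interventions and the Fig. 2 footnote differ on whether follow-up can pass 36 months. The sample size is unaffected.

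The verdict rests on the article's text alone and assumes that the bone-age values are minimums. It warrants correction because it concerns the primary endpoint, not because a bias has been shown.

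**What to change.** The sponsor should reconcile the Fig. 2 footnote, Study procedures and Planned final analyses to a single definition of near final height, with each bone-age value written directly beside its sex instead of in a list to be matched in order. If the growth-rate-only wording is shorthand, it should refer to the full definition. The lower age range for girls in the Inclusion criteria is consistent with the ordering in Planned final analyses, but the sponsor must confirm the values. Because near final height also bears on the end of follow-up and of GH treatment, that choice is not one for this review.

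The text should also say whether the scheduled near-final-height X-ray is the film used to confirm the bone-age criterion, if that is the intention. The two statements on the 36-month limit should be reconciled at the same time.

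The cost is a wording correction, a check that Protocol V2.0, the case report form and the SAP carry the same definition, and a note to sites. According to Trial status, no patient had been recruited at publication, so a correction at that time would not have required reclassifying anyone.
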